## 10.2. Serious Adverse Event Definition

A Serious Adverse Event (SAE) is defined as an adverse event that:

- led to death
- led to a serious deterioration in the health of the participant, that either resulted in:
  - a life-threatening illness or injury
  - a permanent impairment of a body structure or a body function
  - in-patient hospitalisation or prolongation of existing hospitalisation (defined as greater than 24 hours in hospital)
  - medical or surgical intervention to prevent life-threatening illness or injury or permanent impairment to a body structure or a body function
- led to foetal distress, foetal death or a congenital abnormality or birth defect.

Planned hospitalisation for a pre-existing condition, or a procedure required by the protocol, without serious deterioration in health, is not considered a SAE.

## 10.3. Anticipated Adverse Events

Within the context of BS EN 13612 (2002) and with the knowledge that the excision of tissue will not be outside of the normal practice as deemed appropriate by the PI, the LightPath® Imaging System cannot be associated with adverse events.

The radiopharmaceuticals used in this study are commonly administered at doses required by this protocol with no reported safety issues. Therefore, no AEs related to the administration of radiopharmaceuticals are anticipated.

The following are known complications of breast surgery, sentinel lymph node biopsy (SLNB) and axillary lymph node dissection (ALND) (Vitug and Newman 2007), and are anticipated procedure-related AEs:

- Wound infection (including cellulitis and abscess formation)
- Seroma
- Haematoma
- Pain
- Lymphoedema
- Neurosensory disturbance in the upper limb
- Allergic reaction to blue dye

The participants may have additional cavity shavings compared to standard of care surgery at the Investigator's discretion. Risks added by this minor addition to the already major procedures of standard of care surgery are expected to be minimal.

#### 10.4. Adverse Event Severity

AE severity will be assessed according to the Common Terminology Criteria for Adverse Events (CTCAE) version 4.0 (U.S. Department Of Health And Human Services 2009):

- Grade 1 Mild; asymptomatic or mild symptoms; clinical or diagnostic observations only; intervention not indicated.
- Grade 2 Moderate; minimal, local or non-invasive intervention indicated; limiting age-appropriate instrumental activities of daily living.
- Grade 3 Severe or medically significant but not immediately life-threatening; hospitalisation or prolongation of hospitalisation indicated; disabling; limiting self-care activities of daily living.
- Grade 4 Life-threatening consequences; urgent intervention indicated.
- Grade 5 Death related to AE

It is important to distinguish between serious and severe AEs. Severity is a measure of intensity whereas seriousness is defined by the criteria under 10.2. An AE of severe intensity may not be considered serious.

#### 10.5. Relationship to Study Procedures

The following definitions will be used to assess the relationship between an AE and the study procedures, radiopharmaceutical, or operational procedure. The CI will specify in each case if the event relates to the study procedures, to the radiopharmaceutical, and / or to the surgery procedure.

##### Not Related

The event can be determined with certainty to have no relationship to the study procedures.

#### Unlikely to be Related

There is no evidence for the causal relationship between the study procedures and the AE. The event was likely produced by other factors such as the subject's clinical state, surgical / therapeutic intervention, or concomitant therapy but for which relationship cannot be ruled out.

#### Possibly Related

The event has a reasonable temporal relationship to the study procedures and follows a known response pattern to the study procedures. However, a potential alternate aetiology may be responsible for the event, such as the subject's clinical state, surgical / therapeutic intervention, or concomitant therapy.

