### 7.2.2. Risk to participants

The LightPath® Imaging System is non-radiation emitting. Risks to participants in this study are associated with radiation exposure from the  $^{18}\text{F}$ -FDG and its administration procedure. In addition, the LightPath® images may lead to extra cavity shavings.

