#### Probably Related

The event follows a reasonable temporal sequence from the time of the study procedures and/or follows a known response pattern to the study procedures and was unlikely to have been produced by other factors such as the subject's clinical state, surgical / therapeutic intervention, or concomitant therapy.

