#### Related

The event follows a temporal sequence from the time of the study procedures and follows a known response pattern to study procedures and either occurs immediately following study procedures, or improves on stopping the study procedures, or reappears on repeat exposure to the study procedures.

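### The causality scale in Section 10.5 is out of order: a known response pattern is mandatory for *Possibly Related* but optional for the stronger *Probably Related*

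*Protocol*

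**What the plan says.** Section 10.5 of the protocol gives five grades of relationship and asks for an attribution in each case, separately to study procedures, radiopharmaceutical and surgery. Three definitions matter here.

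- *Possibly Related*: "The event has a reasonable temporal relationship to the study procedures and follows a known response pattern to the study procedures". It then allows that another cause, including surgery, may be responsible.
- *Probably Related*: a reasonable time sequence "and/or follows a known response pattern to the study procedures and was unlikely to have been produced by other factors", with surgery again among those factors.
- *Related*: "The event follows a temporal sequence from the time of the study procedures and follows a known response pattern to study procedures", plus one of immediate onset, improvement on stopping, or recurrence on re-exposure.

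Section 10.3 says of the device that "the LightPath® Imaging System cannot be associated with adverse events", within the context of a cited standard and on the understanding that excision stays within normal practice. Of the tracers it says that "no AEs related to the administration of radiopharmaceuticals are anticipated". The same section lists known complications of breast and axillary surgery and adds: "The participants may have additional cavity shavings compared to standard of care surgery at the Investigator's discretion".

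**The concern.** A causality scale should ask for more evidence as the grade rises. Here the weaker grade makes a known pattern compulsory and the stronger grade does not. The events most affected are those without a precedent, which attribution on each event is meant to pick up.

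The grade has consequences. Section 10.1 follows events judged related to a study procedure until resolution or for 30 days. Section 10.6 waives reporting for events put down to standard care and judged unrelated to any study procedure. The safety analysis in 11.7.3 is headed as study-related adverse events. If a rule pushes uncertain events downward, they may be followed less and may not appear in the results.

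The device sentence in 10.3 raises a second problem. The investigator is asked for a judgement on each event while the protocol already states the answer for one of the exposures.

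**Working it through.** No rate, sample size or error level enters this point and the plan states no figure to reproduce, so the check is on the logic of the definitions.

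Inputs, all from Section 10.5:

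- T: the timing fits.
- K: the event follows a known response pattern to the study procedures.
- U: other causes are unlikely.
- X: immediate onset, improvement on stopping, or recurrence on re-exposure.

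The grades as written:

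- *Possibly* = T and K, with another cause allowed.
- *Probably* = (T or K) and U.
- *Related* = T and K and X. It contains no test for another cause.

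For a well-timed event (T true):

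| K | U | Highest grade available |
|---|---|---|
| yes | yes | *Probably*, or *Related* if X |
| yes | no | *Possibly*, or *Related* if X |
| no | yes | *Probably* |
| no | no | none of the three; falls to *Unlikely* |

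The last two rows show the fault. With no known pattern, moving from other causes being unlikely to another cause being plausible takes the event from *Probably* straight to *Unlikely*, skipping *Possibly*. *Unlikely* is itself a poor fit: it requires no evidence of a causal link and an event likely due to something else, neither of which follows from another cause being merely plausible.

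The last row can readily occur. Every participant has breast surgery. 18F-FDG is given about 145 minutes before specimen imaging (8.6.2), hence on the day of surgery, and the definitions themselves name surgery as an alternative cause.

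Next, K for each exposure the study adds:

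- Imaging device. Taken literally, 10.3 leaves no known pattern, so K is false and *Possibly* and *Related* cannot be reached. *Probably* remains open under the wording of 10.5, but 10.3 points the assessor away from it.
- Tracers. Section 10.3 states only an expectation. Known hypersensitivity to 18F-FDG is an exclusion criterion (7.5), and 10.6 treats infections that may reflect bacterial endotoxin as events of special interest. K can be true; only a novel tracer event lands in the last row.
- Extra cavity shavings. The surgical complications listed in 10.3 supply a pattern, so K can be true.

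**The case against.** A reader might infer something stronger: that the definitions together with 10.3 close both grades for everything the study adds, that no device-related event could ever be reported, and that the safety results are therefore uninformative. The documents do not support this.

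- That no tracer events are anticipated does not mean that no tracer pattern is known, and 7.5 and 10.6 show that the protocol recognises some.
- Extra shavings have listed complications.
- *Probably Related* needs no pattern. An event between injection and incision, for example, could not be due to the surgery.
- Serious events are reported and followed whatever their grade (10.7), events of special interest are handled in the same way (10.6), and all device deficiencies are recorded (10.8).
- The reporting waiver in 10.6 requires an event to be unrelated to any study procedure. An event graded *Unlikely*, where a relationship is not excluded, is not clearly covered.

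Nor does the device sentence plainly contradict 7.2.2, which says "In addition, the LightPath® images may lead to extra cavity shavings". Section 10.3 acknowledges the same shavings, and both sections treat them as an indirect risk. The device sentence is also qualified and concerns a system that images excised tissue.

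All of this stands, and it narrows the point. It does not answer the ordering fault, nor does it give a novel, well-timed event with a plausible alternative cause a proper grade. The qualifier in 10.3 softens the device sentence but leaves it categorical.

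**Conclusion.** The point holds in limited form. The scale is not ordered, and one of the four combinations open to a well-timed event (no known pattern, another cause plausible) is pushed to *Unlikely*. For the device, 10.3 also prejudges the attribution that 10.5 requires. The effect falls mainly on non-serious, unprecedented events around surgery: they lose related-event follow-up under 10.1 and can be lost from the summary in 11.7.3.

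This rests on two assumptions. The first is that investigators apply the definitions as written. The second is that *Unlikely* is not counted as related for follow-up and summary; Section 10 does not state the cut-off. The protocol gives no expected adverse event rate, so the number of misgraded events cannot be estimated. The correction should be made because it is cheap and because the definitions are applied as events occur, so it cannot wait for the analysis stage.

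**What to change.** Three wording changes, to be reconciled together:

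1. In 10.5, define *Possibly Related* as a reasonable temporal relationship and a plausible link to a study procedure, whether or not a known response pattern exists, with another cause allowed. A known pattern then supports the grade but is not required.
2. Keep *Related* at least as strict as *Probably Related*. Its pattern condition should not simply be dropped: that definition has no test for other causes, so without the pattern condition the top grade would be easier to reach than the one below it.
3. In 10.3, restate the device sentence as an expectation that the system will not directly cause adverse events, with relatedness judged for each event under 10.5.

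The cost is a protocol amendment and some extra work. Because all participants have surgery, more perioperative events may be classed as possibly related and need follow-up. Requiring a plausible link as well as timing limits that increase.

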#### Probably Related

The event follows a reasonable temporal sequence from the time of the study procedures and/or follows a known response pattern to the study procedures and was unlikely to have been produced by other factors such as the subject's clinical state, surgical / therapeutic intervention, or concomitant therapy.

#### Related

The event follows a temporal sequence from the time of the study procedures and follows a known response pattern to study procedures and either occurs immediately following study procedures, or improves on stopping the study procedures, or reappears on repeat exposure to the study procedures.

### 10.6. Adverse Event Reporting

AEs occurring from the first study procedure until the end of follow-up will be reported by completing the relevant section of the CRF. AEs judged by the CI to be related to the standard care of the participant and unrelated to any study procedure do not require to be reported.

The following information will be recorded in the adverse event section of the CRF:

- The signs, symptoms, or diagnosis of the event
- The date and time of onset and resolution of the event
- The adverse event severity using the criteria outlined above
- The relationship of the event to the study procedures as outlined above
- The seriousness of the event as outlined above;
- A list of any required therapy, medication, treatment, or diagnostic procedure
- Any additional data which might be relevant to the event.

The CI is responsible for the appropriate medical management of all adverse events and for the personal safety and wellbeing of the participants.

In addition, a positive sterility test result post-release for a batch which has been administered to patients will be classified as an Adverse Event of Special Interest (AESI). For this reason, infections that could be signs and symptoms possibly related

to bacterial endotoxin will be considered AESI and be immediately reported to the Sponsor even if non-serious. All AESI must be reported in the same manner as SAE reporting and will be handled in the same way.

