## **10. Adverse Events Definition and Reporting**

### **10.1. Adverse Event Definition**

An adverse event (AE) is any untoward medical occurrence in a participant or participant administered a pharmaceutical product (or surgery in this study) and which does not necessarily have a causal relationship with this treatment. An AE can therefore be any unfavourable and unintended sign (including an abnormal laboratory finding), symptom, or disease temporally associated with the use of a

medicinal product as part of a clinical study, whether or not related to the medicinal product (or surgery).

All AEs, either observed by the Investigator or reported by the participant, must be reported immediately, and no later than 24 hours of becoming aware of the event, to the Sponsor. To report an AE, the Principal Investigator (PI) will complete an AE report form or other relevant form located in the Case Report Form. The report will include the following information: nature, severity, date of onset, duration, course and history of the adverse event/adverse device effect and causality.

Recording of AEs will begin with the commencement of the first study procedure. As all study procedures are completed prior to the end of surgery and the radiopharmaceuticals have short physical half-lives, AE recording will conclude when the subject is discharged from hospital, or 24 hours following the first study procedure (whichever is sooner). Any adverse event identified in this period considered by the Principal Investigator (PI) to be related to a study procedure will be followed until resolution or for 30 days, whichever is sooner.

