### **10.7. Serious Adverse Event Reporting**

Any serious adverse event must be reported to the sponsor and, where required, the relevant ethics committee within 24 hours of the onset of the event. Full details of the event, treatment, and an assessment of the relationship to study procedures must be provided in the report.

All serious adverse events will be followed until they are resolved or for 30 days after the subject's participation in the clinical study ends.

The CI should institute appropriate therapeutic and follow-up measures in accordance with good medical practice but should notify the monitor of such actions and record them in the subject's Case Report Form.

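### Sections 10.1 and 8.6.9 call for every AE to be captured, section 10.6 exempts some by attribution, and the status of LightPath-directed shavings is undefined, so non-serious complications after them may go unrecorded

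*Protocol*

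**What the plan says.** Section 10.1 defines an AE as something that "does not necessarily have a causal relationship with this treatment". It then sets a rule without exception: "All AEs, either observed by the Investigator or reported by the participant, must be reported immediately", with an outer limit of 24 hours from awareness. It names the instrument, "To report an AE, the Principal Investigator (PI) will complete an AE report form or other relevant form located in the Case Report Form", and asks for causality among the details. Section 8.6.9 adds, for the day of surgery, that details of any AE are recorded.

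Section 10.6 also works through the CRF but removes a class of events: AEs that the CI attributes to standard care and judges "unrelated to any study procedure do not require to be reported".

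Section 10.5 asks the CI to say whether each event relates to the study procedures, the radiopharmaceutical or the surgery, and gives a five-step relatedness scale. Its lowest step reads: "The event can be determined with certainty to have no relationship to the study procedures". Section 10.3 lists wound infection, seroma, haematoma and pain among the complications of breast and axillary surgery that "are anticipated procedure-related AEs". It also states that the device itself cannot be associated with AEs, provided that tissue excision stays within normal practice.

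Section 10.7 requires every serious adverse event (SAE) to be reported "within 24 hours of the onset of the event". Section 11.7.3 summarises AEs on the ITT population.

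**The concern.** The decision on whether an event is related should be a variable in the safety data. Under section 10.6 it also decides whether an event enters those data at all. The events most exposed to this are complications of the extra cavity shavings. They are the surgical consequence of acting on the images, and they are taken from the same cavity in the same operation as the planned excision. A haematoma after such a shaving looks like a haematoma after the excision alone.

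At stake is whether the section 11.7.3 summary covers the non-serious harm that may follow from acting on LightPath images. Two investigators working in good faith from different sections would produce different summaries from the same patients. The trial is open with a single arm, so no comparison group would reveal that events were missing. Attribution can be reviewed later, but an event that was never written down cannot be reliably recovered.

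**Working it through.** No figure in the protocol bears directly on this point, so the check is mainly a comparison of sections.

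**1. Do the two rules govern the same act?** Section 10.1 sends AEs to the sponsor through a form in the CRF. Section 10.6 reports AEs by completing the relevant part of the CRF. The instrument is the same, so the conflict cannot be resolved by reading one section as expedited reporting and the other as recording.

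**2. Which events are treated differently?** The exemption needs both conditions.

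| CI's judgement or event type | 10.1 | 10.6 or 10.7 |
|---|---|---|
| Related to standard care and unrelated to any study procedure, non-serious | Report | Exempt (10.6) |
| Related to standard care, but not ruled unrelated to study procedures | Report | Report (10.6) |
| Related neither to standard care nor to study procedures | Report | Report (10.6) |
| SAE, any cause | Report | Report (10.7) |
| Infection possibly due to bacterial endotoxin, even if non-serious | Report | Report as event of special interest (10.6) |

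The conflict lies in the first row only.

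**3. Can a complication after a LightPath-directed shaving fall in that row?** This depends on what the shaving is, and the protocol does not say.

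- *If it is a study procedure:* Not Related requires certainty. With one shared cavity that certainty is hardly attainable, so the event stays reportable. Section 7.2.2 (extra shavings named as a participant risk) and section 10.3 (shavings additional to standard-of-care surgery) lean this way.
- *If it is surgery:* the study procedures reduce to the imaging and the tracer. Section 10.3 says that the device cannot be associated with AEs and that none are anticipated from the radiopharmaceuticals. The Unlikely, Possibly and Probably categories in 10.5 all name surgical intervention as an alternative cause. The CI can then judge the event unrelated, and it is exempt. The separate surgery heading in 10.5 and the title of section 7.2.1, which speaks of directed surgical procedures, lean this way.

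Both readings are open on the text.

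**4. How many women are exposed?** Section 11.6.2 plans on 20% positive margins, 95% sensitivity and 90% specificity. At patient level the LightPath-positive share is then 0.20 × 0.95 + 0.80 × 0.10 = 0.19 + 0.08 = 0.27, and 0.27 × 60 = 16.2, or about 16 women. Not all would be shaved, because the surgeon has discretion and more tissue must be available. The protocol gives no complication rate, so this count cannot be turned into a number of lost events.

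**5. The SAE clock.** An SAE is also an AE, so both clocks apply. Put onset at hour 0 and awareness at hour h. The deadline is h + 24 under 10.1 and 24 under 10.7. If h exceeds 24, the second deadline has passed before anyone knows of the event.

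**The case against.** The best defence is that section 10.6 is narrow and the rest of the protocol limits the damage. Both conditions must hold. If harm from the added shaving and from the planned excision cannot be told apart, the CI cannot call the event unrelated, and the certainty required for Not Related keeps it in the data. Section 10.7 captures all SAEs and section 10.6 itself captures endotoxin-type infections. The Schedule of Events row and the subheading in 11.7.3 both speak of study-related AEs, so a related-only scope may be what the sponsor intended. Section 10.1 could then be narrowed instead.

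Much of this stands. A reader might infer that the safety table would hold only events already judged study-related, or that Not Related would be almost unused. The documents do not support either: events graded Unlikely, SAEs of any cause and events tied to neither standard care nor the study remain reportable. A reader might also infer that complication rates would be biased against those of ordinary wide local excision, but no such comparison is planned. Nor is there support for applying an assumed complication rate to all 60 women: the documents state no rate, and only some of the women would have a directed shaving.

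Two parts do not stand. The certainty argument works only if a directed shaving is a study procedure, which the protocol leaves open. Narrowing 10.1 to study-related events would leave the same question open, so non-serious complications of added shavings could still be left out.

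**Conclusion.** The contradiction is real and should be removed. Its reach is limited to non-serious events that the CI judges both due to standard care and unrelated to any study procedure. Within that class the important cases are haematoma, seroma, pain and wound problems after a LightPath-directed shaving. They may be absent from the 11.7.3 summary, depending on the section the site follows, on how the shaving is classed and on the CI's attribution.

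The loss is possible, not certain, and its number cannot be given from the documents. The AE window is itself stated in two ways: the earlier of discharge and 24 hours after the first study procedure in 8.7, 8.8.1 and 10.1, but the end of follow-up in 10.6. That is a separate matter, though the shorter window would leave fewer events to lose. The SAE clock in 10.7 is a further, independent inconsistency and adds no weight to the main point.

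**What to change.** - Reconcile 8.6.9, 10.1, 10.6 and 11.7.3 so that every AE in the AE window is recorded on the CRF, with relationship given separately for study procedure, radiopharmaceutical and surgery. Section 10.5 already provides these three headings.
- State in 10.5 that a LightPath-directed cavity shaving counts as a study procedure for attribution.
- In 11.7.3, summarise all AEs and show related AEs as a subset.
- If the exemption in 10.6 was meant to spare the sponsor routine notifications, limit it to expedited reporting and say that it does not affect recording.
- Separately, reconcile the 24-hour SAE clock in 10.7, which runs from onset, with 10.1, which runs from awareness.

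The cost is a wording amendment and a few more CRF entries. Sample size, visits and the primary analysis are unaffected.
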